**8.2 Procedures for assessing Efficacy****8.2.1 Seizure outcomes**

At each clinic visit scheduled per routine practice, and any unscheduled clinic visit, the number of seizures, date of first seizure, and date of most recent seizure experienced since previous follow-up visit (or baseline visit if attending the first clinic visit) will be recorded in the CRF. These data will be

used to calculate the primary outcome measure (time to 6-month remission from seizures) and seizure related secondary outcome measures (time to 12-month remission from seizures, time to first seizure).

At each clinic visit scheduled per routine practice and at any unscheduled clinic visit, the date of failure of randomised AED treatment and reason for failure will be recorded in the CRF if relevant. This data will be used to calculate the secondary outcome measure (time to treatment failure).

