## 3.3 Objectives and Outcome Measures/Endpoints

Table 1: Summary of Objectives, Outcome Measures and Timepoints

| Primary Objectives                                                                                                               | Outcome Measures                                          | Timepoint(s) of evaluation of this outcome measure                                   |
|----------------------------------------------------------------------------------------------------------------------------------|-----------------------------------------------------------|--------------------------------------------------------------------------------------|
| To determine if carbamazepine or levetiracetam are superior to no AED with respect to time to 6-month seizure remission.         | Time to 6-month seizure remission based on seizure report | 3, 6, 12 months and annually thereafter - 'when was last seizure' question in clinic |
| To determine if a PBS intervention is superior to standard care with respect to 3-month sleep problem frequency measured by CSHQ | Total sleep problem score as measured by the CSHQ         | At baseline and 3 months                                                             |
| Primary Economic Objective †                                                                                          | Outcome Measures                                          | Timepoint(s) of evaluation of this outcome measure                                   |
| To estimate the cost-utility of carbamazepine, levetiracetam and PBS                                                             | Total costs; and quality-adjusted life years (QALYs)      | Resource use and utility questionnaires at baseline, 3, 12 months and annually       |

† This has no implications for sample size calculation

|                                                                                                          |                                                                                                                                                                                     | thereafter; routine hospital data at the end of the trial                        |

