**8.1.2 Schedule for Follow-up**

The expected duration of follow-up for each participant is between a minimum of 12 months and a maximum of 48 months, depending on the time of recruitment. All participants will be followed up whether they are still taking their allocated treatment or not. Where participants default from hospital follow-up, additional information will be sought at the end of the trial from GPs who will be the main prescribers of AEDs in this trial, and where necessary participants will be contacted directly for follow up information.

Participants will be followed up as per routine clinical practice and typically at 3, 6, and 12 months and annually thereafter, where applicable. Participants will be seen at other times as clinically indicated.

A visit window for the 3 month visit of +/- 2 weeks is allowed. Visit windows are not prescribed for the 6, 12 months or annual visits after that. A delegated member of the research team should complete the 'follow-up CRF' for the 3, 6, 12 month and annual visits. The visit which occurs at the nearest timepoint will be taken to be the record of the 3, 6, 12 months or other annual visits from randomisation.

In the event of an early trial termination, the schedule for follow up activities (including actigraphy and qualitative interviews) will be shortened accordingly to 6 months post-randomisation. This will occur following agreement by the TMG, IDSMC and Sponsor.

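### Count, first date and last date per visit interval cannot always show whether or when a 6-month remission occurred, chiefly once visits are annual after month 12

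*Protocol*

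**What the plan says.** Section 8.2.1 of the protocol has the CRF record "the number of seizures, date of first seizure, and date of most recent seizure experienced since previous follow-up visit". This is done "At each clinic visit scheduled per routine practice, and any unscheduled clinic visit", and the section names these data as the basis for time to 6-month remission, time to 12-month remission and time to first seizure. Table 1 (section 3.3) is narrower: for all three outcomes it gives as source a clinic question, "when was last seizure".

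Section 8.1.2 places visits "typically at 3, 6, and 12 months and annually thereafter, where applicable", with follow-up lasting "between a minimum of 12 months and a maximum of 48 months, depending on the time of recruitment". It adds that "Visit windows are not prescribed for the 6, 12 months or annual visits after that" and that "Participants will be seen at other times as clinically indicated". Section 11.5.1 analyses the interval in days from randomisation to a 6-month remission, by Kaplan-Meier curves and a Cox model. The protocol nowhere asks for the dates of seizures between the first and the last, or for seizure-free periods.

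**The concern.** A 6-month remission is a gap between consecutive seizures, so dating it needs the dates on either side of the gap. Three items per interval supply those dates when intervals are short. After month 12 the scheduled interval is 12 months, long enough to hold a full 6-month remission between the first and last recorded seizures.

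The analysis plan can set a rule for ambiguous records, but it cannot restore dates that were never collected. The children concerned are those still having seizures, so the ambiguity would be commoner in whichever arm has more seizures. Under the planning assumption that is the no-AED arm. The outcome at stake is the primary one for the drug comparison.

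**Working it through.** **Inputs.** Recorded items: section 8.2.1. Visits at 0, 3, 6, 12, 24, 36 and 48 months: section 8.1.2 and Table 2. Probability of being without remission at 6 months, 0.57 on control and 0.37 on drug: section 11.3.1. The protocol gives no seizure rates and no frequency of unscheduled visits, so anything resting on these is an assumption.

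**The plan's own figure.** Comparing 0.57 with 0.37 at two-sided 5% and 80% power gives 97 per group, as stated. The ratio ln(0.57)/ln(0.37) = 0.565 agrees with the stated 0.57. The sample size is not in dispute; the two proportions only calibrate the simulations below.

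**What the record determines.** Let F and L be the first and last seizure dates in an interval.

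- The gap before F is known from the last seizure previously recorded, and the gap after L is known up to the visit.
- With two seizures the inner gap is exactly L − F.
- With three or more, the inner gaps are unknown, but a 6-month gap can be hidden only if L − F is at least 6 months. If L − F is shorter, everything is determined.

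Ambiguity therefore needs all of these: no earlier 6-month remission, an interval longer than 6 months, at least three seizures in it, L − F of at least 6 months, and no unscheduled visit that splits it. The scheduled gaps up to month 12 are 3, 3 and 6 months, but with no window at the 6- and 12-month visits an earlier interval can also exceed 6 months.

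**Example.** Visits at months 12 and 24, in a child not yet in remission:

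- Seizures at 13, 14, 21, 23: the gap from 14 to 21 is 7 months, so remission is reached at month 14 + 6 = 20.
- Seizures at 13, 16, 20, 23: the gaps are 3, 4 and 3 months, so there is no remission.

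Both are recorded as n = 4, first = 13, last = 23. All that is known is that either a remission was reached between F + 6 = 19 and L = 23, or none was reached by 23.

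**Share of 12-month intervals affected.** Assume n seizure dates uniform over 12 months. With r = 6/12 = 0.5:

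- P(L − F ≥ 6 months) = 1 − [n·r^(n−1) − (n−1)·r^n]
- P(an inner gap of 6 months or more really exists) = (n−1)·r^n

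| n | L − F ≥ 6 months | hidden 6-month gap |
|---|---|---|
| 3 | 50% | 25% |
| 4 | 69% | 19% |
| 5 | 81% | 12.5% |
| 10 | 99% | 0.9% |

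So half of three-seizure intervals and 31% of four-seizure intervals remain fully determinable.

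**Share of children affected, no unscheduled visits.** Poisson seizures with a constant rate, with or without gamma variation between children; 43% or 63% seizure-free over the first 6 months (1 − 0.57 and 1 − 0.37); follow-up uniform over 12 to 48 months. Children with at least one ambiguous interval after month 12:

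| Variation between children | 43% seizure-free (no AED) | 63% seizure-free (drug) |
|---|---|---|
| none | 1.6% | 0.1% |
| gamma, shape 1 | 12.7% | 2.7% |
| gamma, shape 0.5 | 21.7% | 6.3% |

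**With unscheduled visits.** In runs with gamma shape 0.5 to 2 and a constant rate or one falling 3% a month (shape 2 with the falling rate not included), 5% to 19% of the no-AED arm was affected with no extra visits. If each seizure had a 25% chance of prompting a visit within 1.5 months, this fell to 3% to 8%; at 50% it fell to 1% to 2%. These visit probabilities are assumptions.

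**Effect on the hazard ratio** (drug against no AED; the planning value in this direction is 1/0.565 = 1.77). In the same runs, counting only gaps that the record demonstrates changed the hazard ratio by less than 0.01, for example 1.787 against 1.778. Crediting every ambiguous interval as a remission moved it from 1.79 to 1.57 at worst with no extra visits, and by about 0.04 at most with the 25% visit probability.

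**The case against.** The strongest reply is that unscheduled visits are part of the data collection. Section 8.2.1 records the same items there, Table 2 marks seizure review in that column, and section 9.2.3 expects treatment to be reconsidered when seizures recur. A child with several seizures spread over half a year is the one most likely to be seen between annual visits. This stands as a reason to expect far fewer cases than the no-visit figures suggest. It does not remove the gap, because those visits happen only when clinically indicated and a primary outcome should not depend on them.

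Other points stand as well. The follow-up CRF is not shown and might hold more than section 8.2.1 lists. Data queries and access to source records (section 13.4) could recover some dates. Children recruited in the last year of recruitment have under 24 months of follow-up. Under the early-termination provision in section 8.1.2, follow-up would shorten to 6 months and the issue would largely disappear.

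Three stronger readings are tempting and not supported:

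- A reader might infer that remission is undeterminable for every child with three or more seizures in an interval. It is undeterminable only under all the conditions listed above.
- A reader might infer that the treatment comparison is materially biased. The protocol states no derivation rule for ambiguous records, and under a rule that counts only demonstrable gaps the change was negligible.
- A reader might infer from Table 1 that time to first seizure cannot be obtained. Section 8.2.1 collects the first date, so that outcome is unaffected; Table 1 is merely incomplete.

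**Conclusion.** The gap is real, narrow and worth closing. The logical part rests on the protocol alone: two seizure histories with different primary outcomes can give identical records. The size does not. With no extra visits, roughly 0.1% to 22% of children could be affected, the range being wide because seizure rates and their spread between children are assumed; it is markedly lower if seizures prompt visits. Under the planned effect the share is larger in the arm with more seizures. The effect on the hazard ratio depends on a rule that the protocol does not state and may be small, so this is a should-fix and not evidence of a compromised primary analysis. Time to 12-month remission is touched only where an interval exceeds 12 months.

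**What to change.** - In section 8.2.1 and the follow-up CRF, for any interval longer than 6 months, record the start and end dates of any seizure-free period of 6 months or more since the last visit, or record all seizure dates. With every date recorded, the undetermined share is zero by construction.
- For intervals already recorded, query sites where the count is three or more and first-to-last is at least 6 months. Do this early, since recall of dates fades.
- Reword the source in Table 1 so that it matches section 8.2.1.

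The cost is one extra CRF item, a limited number of data queries and a small recall burden on parents. Sample size, visit schedule and treatment are unchanged.

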### **8.2.2 Health Related Quality of Life**

The scores obtained for the CHEQOL questionnaire (1) throughout the trial can be used as a subjective measure of efficacy. The parent/primary carer will complete a proxy version of the questionnaire while the child (if  $\geq 8$  years) completes the CHEQOL child version. Both questionnaires will be delivered on paper at the specified timepoints (see Table 2: schedule of trial procedures).

### **8.2.3 Strengths and Difficulties Questionnaire**

SDQ is a brief emotional and behavioural screening questionnaire that will be used to compare children across the different treatment groups. The scores obtained from this questionnaire throughout the trial can be used as a subjective measure of efficacy. SDQ will be completed by the parent/primary carer at the specified timepoints (see Table 2: Schedule of trial procedures).

### **8.2.4 Parent self-efficacy measure**

The scores obtained for the Parenting Self-Agency Measure (PSAM) questionnaire (3) throughout the trial will be used as a subjective measure of parental efficacy. The parent/primary carer will complete the questionnaire at the specified timepoints (see Table 2: schedule of trial procedures).

A recent review showed that PSAM was a reliable domain for specific measures of parental efficacy. Although it came second to another measure called CAPES-SE in overall 'quality', the CAPES-ES was 20 items long (compared to PSAM which is 5) and also covered things that are already being tapped by other measures used in this trial (e.g. child behaviour challenges). Additionally, CAPES-SE focuses on how confident parents feel in managing these 'problems' rather than about parenting more broadly, which is what PSAM will be delivering and what we aim to capture (19, 20).

### **8.2.5 Sleep**

#### **8.2.5.1 Subjective Sleep**

The primary sleep outcome uses the CSHQ (21). This is a standardised, widely used questionnaire to assess sleep problems in school-age children referenced in over 600 publications. Parents/primary carers will complete a paper-based questionnaire when they attend clinic. Parents/primary carers will be asked to recall events over the past typical week indicating the frequency of occurrence of a number of sleep related behaviours. In addition to information about sleep timing, the questionnaire gives both an overall sleep disturbance score and eight subscale scores: bedtime resistance, sleep onset delay, sleep duration, sleep anxiety, night-wakings, parasomnias, sleep-disordered breathing and daytime sleepiness, reflecting key areas of clinical concern.

#### **8.2.5.2 Actigraphy**

Although previous studies have demonstrated impaired sleep quantity and quality of parents of children with epilepsy (22), none have employed objective measures to demonstrate whether the impairment is related to a perceived or a measurable deficit in sleep parameters. Actigraphy is a wrist-worn, accelerometer-based method of objective sleep assessment widely used in research and clinical practice and has been used successfully with children, including those with a range of developmental disorders (23, 24).

Up to 15 dyads (child and primary carer) from each of the 6 final trial subgroups will both wear the watches (actigraphs) for 1 week at baseline, 3 and 12 months during the trial. However, only the data from a purposeful sample of 10 dyads from each group will be analysed; this is to account for any drop outs or incomplete data. Actigraphy data will let us look at baseline sleep patterns, the relationship between the primary carer and the child's sleep, and the impact of different treatments during the trial. Summary variables of sleep latency, total sleep time and sleep efficiency will be used for analysis. Along with the actigraphs, parents/primary carers will be asked to complete a sleep log that will capture 'lights out', subjective sleep times, when the watch was put on/off, exceptions circumstances, etc. Participants might also contribute to log completion if they have capacity to do so but parents are intended to be the key recorder. The information recorded in the sleep logs will be used to facilitate subsequent analysis of actigraphy data.

When a new participant is selected for actigraphy, the sleep research team at Oxford Brookes University will be notified via email so they can proceed to:

1. Log in to the contacts database and view the participant's name, address, phone number and email
2. Contact the parent/primary carer to arrange a convenient time for the shipping of the actigraph and answer any questions they might have
3. Ship the actigraphy equipment together with instructions in the use of the watches and its return, as well as the sleep log (paper document) and contact details for troubleshooting any problems. The shipment will ideally occur within 1-2 days after randomisation but it is acknowledged that it might not always be the case and it will depend on the timing of randomisation and the availability of the parent/primary carer to receive the package.

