| Other Objectives                                                                                   | Outcome Measures                                                                                                               | Timepoint(s) of evaluation of this outcome measure                                               |
| To determine which sleep parameters change in primary carer and child dyads in different treatment groups | Summary of actigraphy variables (total sleep time/sleep latency/sleep efficiency) averaged over a 1-week period                       | 1 week actigraphy (arranged centrally via Oxford unit) at baseline, 3 and 12 months                     |

|                                                                                                                                                                                          |                                                                             |                                                           |
|------------------------------------------------------------------------------------------------------------------------------------------------------------------------------------------|-----------------------------------------------------------------------------|-----------------------------------------------------------|
| Sub-study Objective                                                                                                                                                               | Outcome Measures                                                     | Timepoint(s) of evaluation of this outcome measure |
| To explore and capture qualitative information relating to children's and their parents' experiences of the decisions and choices they make regarding the treatment and management of RE | Face-to-face/telephone or skype interviews (audio recorded and transcribed) | 2-4 weeks, 6 months and 12 months after randomisation     |

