## **7.5 Randomisation Procedures**

Patients **should not** be randomised until:

- a) Written informed consent has been obtained from an appropriate adult and assent if appropriate obtained from the patient;
- b) All eligibility criteria have been fulfilled and full eligibility has been confirmed by a medically qualified doctor and this has been recorded in the patient's medical notes and on the Eligibility case report form (CRF);
- c) The Baseline CRF has been completed.

All participants will be randomised firstly between carbamazepine or levetiracetam or active monitoring in a 1:1:1 ratio, and secondly between PBS or standard care in a 1:1 ratio (see flow diagram, Figure 1). A subset of participants will be purposively selected to wear an actigraphy watch and participate in the actigraphy sleep monitoring component.

If allocated to carbamazepine or levetiracetam, the randomised treatment should ideally begin on the day of randomisation, or within 14 days of randomisation at the latest. If the participant has been selected to wear an actigraph, the treatment should not commence until the actigraph has been worn for the first week (however treatment should still commence within the 14 day window after randomisation). Carbamazepine or levetiracetam treatment should be sourced via usual NHS arrangements (see section 9).

Participants will be randomised using a secure (24-hour) web-based randomisation programme. Allocation sequences will be computer-generated, and concealed from staff recruiting participants to the trial using a secure internet-based system created and maintained by the CTRC. A personal login username and password, provided by the CTRC, will be required to access the randomisation system; designated research staff will be issued with their personal login and password upon completion of training in the use of the system.

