## **7.6 Who is Blinded to Allocations**

Data analysts will be blinded after assignment to interventions by assignment of randomisation numbers to participants.

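### Actigraphy: fitting 15 watches per group guards against drop-out, but that does not justify analysing only a purposeful 10 and discarding other usable recordings

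*Protocol*

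**What the plan says.** Protocol section 8.2.5.2 provides that "Up to 15 dyads (child and primary carer) from each of the 6 final trial subgroups" wear the watches, and Table 1 in section 3.3 gives the schedule as "1 week actigraphy (arranged centrally via Oxford unit) at baseline, 3 and 12 months". Section 8.2.5.2 then states that "only the data from a purposeful sample of 10 dyads from each group will be analysed", adding that "this is to account for any drop outs or incomplete data". The version 2.0 entry in the chronology of amendments (section 17.2) gives the same two numbers, so the cap is deliberate.

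The data are not only descriptive. Table 1 sets the objective "To determine which sleep parameters change in primary carer and child dyads in different treatment groups", and section 8.2.5.2 lists "the impact of different treatments during the trial" among the uses, alongside baseline sleep patterns and the relation between the carer's and the child's sleep.

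Choosing who wears a watch is a separate and earlier step. Section 7.5 says "A subset of participants will be purposively selected to wear an actigraphy watch". On masking, section 7.6 says "Data analysts will be blinded after assignment to interventions". Section 13.3 has the Oxford Brookes sleep team extract the recordings and identify the periods for sleep analysis, and section 9.1.2 has the same team notified of each allocation to the parent-based sleep intervention (PBS).

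**The concern.** Over-recruiting against drop-out is a reason to aim for at least 10 complete dyads per group. It gives no reason to set aside an eleventh or a fifteenth usable recording, and the protocol makes no provision for using more than 10.

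The word purposeful adds a second problem. It implies selection by judgement, and no rule, timing or responsible person is given. Because the spare dyads exist to cover losses over 12 months, the final 10 cannot be fixed until completeness is known. Completeness arises after randomisation and may depend on allocation, so even a choice made only on completeness can tilt the comparison.

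At stake is the one objective sleep measure in an unblinded trial whose sleep primary outcome is a questionnaire completed by the carer. Precision already paid for is lost, and a reader of the results could not tell how the 10 were chosen.

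**Working it through.** **Where 15 and 10 come from.** The protocol gives no power, standard deviation or attrition rate for actigraphy, so neither number can be reproduced. Going from 15 to 10 implies attrition of 1 − 10/15 = 33.3%. The only attrition rate in the protocol, 12% in section 11.3.1 for the drug comparison, would require 10/0.88 = 11.4, that is 12 dyads per group.

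**Totals.** Worn: 6 × 15 = 90 at most. Analysed: 6 × 10 = 60.

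**Expected loss.** Assume that exactly 15 dyads per group wear watches, that each is unusable with probability d independently of the others, and that X is the number usable.

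- X ~ Binomial(15, 1 − d), so expected usable = 15(1 − d).
- Expected discarded = Σ (x − 10) P(X = x) for x = 11 to 15.
- Share lost = discarded / usable.
- Approximate standard-error factor = √(usable / analysed), where analysed = usable − discarded.

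For d = 0.12, P(X = 15, 14, 13, 12, 11) = 0.147, 0.301, 0.287, 0.170, 0.069. Expected discarded = 5(0.147) + 4(0.301) + 3(0.287) + 2(0.170) + 0.069 ≈ 3.21. Share lost = 3.21/13.2 = 24%. Standard-error factor = √(13.2/9.99) = 1.15.

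| Assumed attrition d | Usable per group | Discarded per group | Share of usable lost | Standard-error factor | P(more than 10 usable) |
|---|---|---|---|---|---|
| 0% | 15.0 | 5.0 | 33% | 1.22 | 100% |
| 12% | 13.2 | 3.2 | 24% | 1.15 | 97% |
| 20% | 12.0 | 2.1 | 17% | 1.10 | 84% |
| 33% | 10.0 | 0.7 | 7% | 1.04 | 40% |

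The last column is the chance, per group, that someone must actually choose which dyads to leave out.

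**What this means for the sleep comparison.** Each sleep arm pools three drug groups: 3 × 15 = 45 dyads without the cap and 3 × 10 = 30 with it. Assume a two-sided 5% level, 80% power and no baseline adjustment. The detectable difference in standard-deviation units is (1.96 + 0.84) × √(2/n):

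- 30 per arm (capped): 0.72.
- 45 per arm (no cap, no attrition): 0.59.
- 39.6 per arm (no cap, 12% attrition): 0.63.

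**Masking, section by section.** Section 7.6 covers data analysts. Sections 9.1.2 and 13.3 together show that the team extracting the recordings is told who was allocated to PBS. Section 8.2.5.2 does not say which of these parties picks the 10. Analyst blinding is therefore only a partial safeguard for that step.

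**The case against.** *The protocol does not say that analysts choose, or that anyone sees outcomes first.* This is right. A reader might infer that analysts may pick dyads after seeing the sleep results. The stated reason implies knowledge of completeness, not of sleep outcomes, and analysts are said to be blinded. What stands is narrower: the text gives no rule and does not exclude a choice made with knowledge of the recordings.

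*The comparison was never a full randomised one.* This is also right. Wearers are purposively selected (section 7.5), consent to this activity (Table 2 footnote), and drop out of the subset if the watch arrives too late after randomisation (section 9.1.1.1). It would therefore be too strong to say that the cap breaks the randomised comparison. It weakens further a comparison that is already selective, and analysing all wearers does not undo the earlier selection.

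*The loss may be small.* If attrition is near the 33% implied by 15 and 10, the cap costs about 7% of usable dyads. Usable data may also be scarce, because both members of the dyad are recorded at three times over 12 months. This is why a range is shown.

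*The SAP may settle it.* A SAP could define usability and the model. It could not analyse all usable dyads without contradicting the cap fixed in the protocol.

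**Conclusion.** The point holds as a minor-to-moderate one. The drop-out reason justifies 15 watches per group. It justifies neither the limit of 10 nor an unspecified judgement about which 10.

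The loss is between about 7% and 33% of usable dyads for attrition between 33% and none, with standard errors about 1.04 to 1.22 times larger. The upper end is a ceiling, reached only with 15 wearers in every group and no drop-out, so the documents do not support saying that a third of the data will be lost. The attrition rates are assumptions. The 12% is borrowed from the drug sample-size calculation, and the others span a plausible range.

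The possible bias cannot be sized from the protocol. It rests on an unstated selection step, and nothing shows that the step would be misused. Actigraphy sits under other objectives, so no primary or secondary outcome and no power statement is affected.

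**What to change.** Replace the sentence in section 8.2.5.2 with:

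> Up to 15 dyads per group will wear the watches so that at least 10 are expected to provide complete data. All dyads with usable recordings will be analysed in their randomised groups, with usability criteria set before the recordings are viewed.

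Report the numbers fitted, usable and analysed in each group. The usability criteria and the model can be left to the SAP.

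The cost is this wording and some extra processing of recordings that are collected anyway. No additional participants or watches are needed.
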